#### Behavioral pre-screening

Based on extensive behavioral pilot testing, inter-subject variability in the rates of stimuli reported as seen/unseen is expected. To ensure a sufficient number of trials for the planned analyses, subjects in the fMRI and M-EEG studies will participate in a behavioral pre-screening session (prior to recruitment for Experiment 1). In this pre-screening, subjects will play the first world of the game, which includes 50 awareness probes (40 faces/objects and 10 blank catch- trials). Subjects who report seeing between 5–32 faces/objects (12.5–80% of probed stimuli) and report seeing stimuli on 4 or fewer blank catch-trials (40% or less) will pass the pre-screening and will be recruited for participation in the full experiments. This procedure is designed to screen- out subjects who consciously perceive too many or too few of the critical stimuli (thus preventing a full analysis of the brain data due to insufficient numbers of trials) as well as subjects who are not careful enough about reporting what they see (i.e., subjects with too many false alarms). Considering the rareness and opportunistic sampling of the population of epilepsy patients undergoing invasive monitoring, no prescreening will be applied in that sample. Behavior in patients is however likely to differ from neurotypicals. Given performance in collected datasets, if necessary, the experiment will be optimized, or else discontinued if behavior does not meet the expected range.

### Overview of operational hypotheses of the theories

Four different hypotheses will be tested in this experiment. The first set of predictions relates to **levels of activations and inter-areal communication** for stimuli reported as seen vs. unseen in the dAT task (see analysis #1 below). GNW proposes that a network of prefrontal and high-level sensory areas should be found for this contrast. Since opposing predictions between GNW and IIT concern mostly prefrontal cortex, we focus the analyses and predictions on this area. Note however that as per GNW prefrontal and parietal cortices as well as the cingulate are part of the global neural workspace. IIT postulates that differences should be present in posterior cortex between category-selective areas and early sensory areas (per IIT, prefrontal cortex activity is not necessary for consciousness, but differences in prefrontal activity may be found in the dAT condition, given that this is a report paradigm with a secondary target detection task). As for inter-areal communication and synchrony, we aim to test the role of integration, and more specifically the areas over which information is integrated/distributed for conscious percepts. Like in Experiment 1, GNW and IIT postulate different nodes (topologies) related to consciously perceiving a stimulus: when subjects report perceiving faces, GNW predicts long-range synchrony between PFC and Fusiform Face Area (FFA); and for consciously perceiving objects, GNW predicts long-range synchrony between PFC and Lateral Occipital Cortex (LOC). The specific topological pattern of synchronization should be present regardless of the task (although its timecourse may be prolonged under task-relevant conditions). Thus, the content specific pattern of synchronization is expected to be found both for stimuli reported as seen in the dAT and for seen stimuli in the go/no-go conditions in the AT tasks. It should, however, be absent on “unseen” trials of the dAT condition, except possibly for a brief and early (earlier than 300 ms) transient (failed ignition). For IIT, on the other hand, if a stimulus such as a face is seen, face selective cells in FFA should be activated and there should be strong bindings (‘relations’ in IIT) among neural units in posterior cortical areas, from FFA down to earlier visual areas (V1/V2), which should translate into synchronization between these areas. By contrast, when an object is seen, object-selective cells in LOC should be activated and there should be strong bindings from LOC down to earlier visual areas (V1/V2), which can be measured as increased synchronization between these areas. These patterns should be present when stimuli are reported as seen in the dAT condition as well as in the go/no-go conditions of the AT task.

A second set of predictions tests **in which brain areas the content of conscious perception can be decoded** (see analysis #2 below). We will first test decoding of faces vs. objects in the AT task, and then subsequently test decoding of faces vs. objects in the dAT-seen and dAT-unseen conditions separately. Location of the stimulus (left/right visual field) will also be decoded first in the AT task and then for dAT-seen and dAT-unseen conditions separately. GNW predicts that conscious content (i.e., category and location) should be decodable from PFC during the time period of ignition (~300–500 ms), while unconscious content should not be decodable from these areas during this time period. IIT predicts that conscious contents should be best decoded from posterior cortex and with activity patterns that should be similar for seen stimuli across the go and no-go conditions in the AT task and for stimuli reported as seen in the dAT task.

A third prediction focuses on the **temporal dynamics of the process leading to a conscious percept** (see analysis #3 below). According to GNW, during the first 250 ms, activity should be similar in reported-seen and reported-unseen trials. After 250 ms, an ignition marks the activation of the global workspace by the stimulus, so higher activation in prefrontal areas for reported-seen trials, compared to reported-unseen ones, should be found during this later time-window. This prediction will only be tested for GNW, as it does not have direct bearings on IIT. Relatedly, we will test a fourth set of predictions about **the likelihood of a stimulus to be consciously perceived** (see analysis #4 below). GNW predicts that higher pre-stimulus activity in PFC should be found in reported-unseen trials compared to reported-seen trials. IIT, conversely, holds that higher pre-stimulus excitability or greater synchrony within the posterior hot zone should increase the chances of a new stimulus to be perceived.

### Planned analyses and expected outcomes

#### 1. Levels of activation and inter-areal communication

GNW postulates that seen relative to unseen stimuli should activate a network of prefrontal and high-level sensory areas, while IIT avers that differences between seen and unseen stimuli should be present in the posterior hot zone, involving category-selective (FFA, LOC) and early sensory areas. We will test those anatomical predictions by evaluating the differential activity in these areas and the synchrony between them. This will be done by comparing the dAT-seen and dAT-unseen trials with an ROI and whole brain approach, separately for faces/objects and blank trials. We will calculate the synchrony between prefrontal ROIs and posterior category-selective areas, as well as between such category-selective regions and early visual areas (V1/V2), for: (a) go/no-go conditions separately, per stimulus category, vs. blanks in the AT task; and (b) dAT-seen and dAT-unseen separately, per stimulus category, in the dAT condition.

GNW and IIT postulate different nodes related to consciously perceiving a stimulus: when subjects report seeing faces or objects, GNW predicts long-range synchrony between PFC and FFA or LOC, respectively. For IIT, activation and mid-range synchrony between FFA or LOC and early visual areas (V1/V2) is expected for seen, but not for unseen trials. For both theories, the patterns of activation and synchronization should be present both when stimuli are reported as seen in the dAT condition and in go/no-go conditions of the AT task, but absent when the stimuli are not seen.

#### 2. Multivariate decoding of category and location—Activation patterns

This analysis will test decoding of faces vs. objects, and left vs. right locations, in the AT, dAT-seen and dAT-unseen conditions, both with and without the ROI for decoding analyses identified in the localizer task. Decoding within an ROI vs. across the whole brain offers complementary advantages (in terms of sensitivity and generalizability across tasks) and we will utilize both strategies, considering positive results in either approach to be indicative of decodability.

According to GNW, decoding of category and location should be found in PFC for all seen trials and should generalize across tasks (AT-go-seen, AT-nogo-seen, dAT-seen), specifically in the 300–500 ms time-window. According to IIT, decoding of category and location should be maximal in posterior cortical areas for all types of seen trials, and decoding should generalize across tasks (AT-go-seen, AT-nogo-seen, dAT-seen) with a maximum in posterior cortical areas.

#### 3. Temporal dynamics of the neural differences between stimuli reported as seen vs. unseen

We will track the neural dynamics of the difference between seen and unseen stimuli by running an ANOVA analysis with Visibility (seen/unseen) and Time (Early: 0–250 ms, Late: 250–500 ms). This analysis will not involve fMRI data due to the temporal precision required. We will test for a main effect of visibility and an interaction, with the latter testing a key prediction of GNW, i.e., a neural ignition for consciously perceived stimuli, reflected by a late (>250 ms) amplitude difference between dAT-seen and dAT-unseen trials. Prior to 250 ms, activation for dAT-unseen stimuli should be similar (if not equal) to dAT-seen activity, reflecting a fast feedforward sweep propagating from posterior to anterior cortices as well as local recurrent processing. The same is true for decoding of content. Therefore, late differences in amplitude in prefrontal areas between dAT-seen and dAT-unseen trials are expected, with little or no differences earlier in time. IIT does not make explicit predictions about the temporal dynamics differentiating seen from unseen conditions.

#### 4. Baseline differences between stimuli reported as seen vs. unseen

Pre-stimulus baseline activity will be compared between dAT-seen and dAT-unseen trials. We will run a logistic regression with the categorical variables seen/unseen and the continuous variable amplitude to test GNW predictions, and the same logistic regression with the continuous variable’s amplitude and synchrony between category selective and early visual areas to test IIT predictions.

GNW predicts higher pre-stimulus baseline activity in PFC for dAT-unseen than for dAT-seen trials. IIT predicts higher pre-stimulus baseline activity in category specific areas, and/or higher pre-stimulus baseline synchrony between category specific areas and lower visual cortices, in dAT-seen than in dAT-unseen trials.

*Pilot data*. This study was piloted for behavior and eye movement patterns. Results can be found on the OSF page (https://osf.io/6vgy3/). Those tests indicated an adequate number and approximately balanced (though variable between subjects) ratio of seen and unseen trials in the dAT condition (“dAT-seen” and “dAT-unseen”), and that nearly all stimuli are seen in the AT condition (“AT-seen”). The pilot eye tracking results demonstrated that subjects are able to maintain fixation while using peripheral attention to play the game; and that neither eye movements nor blink dynamics vary systematically between seen versus unseen trials. Finally, we conducted an analysis of low-level features of the video game and were able to rule out many potentially confounding variables related to the game dynamics and visual display, showing that by and large they did not contribute to the visibility of the stimulus.

### Data collection procedures for Experiments 1 and 2

#### 1. Functional Magnetic Resonance Imaging (fMRI)

Imaging will be conducted at the Yale Magnetic Resonance Research Center (MRRC) in New Haven and at the Donders Centre for Cognitive Neuroimaging (DCCN), of Radboud University Nijmegen in Netherlands. Both centers have a Siemens 3T Prisma research scanner (Siemens, Erlangen, Germany) with high performance gradients (max. gradient strength 80mT/m, 200mT/m/s rise time, 100% duty cycle), 32-channel parallel imaging and a 32-channel head coil.

The systems are equipped with behavioral testing apparatus including visual display on a screen projected to a mirror fixed to the head coil, a button response system, and software for display and recording of behavioral tasks synchronized with the MRI data acquisition. At Donders Institute, stimuli will be presented on an MRI compatible Cambridge Research Systems BOLDscreen 32” IPS LCD monitor (resolution 1920 x1080 at 60Hz; viewing distance ~134cm). Psychology Software Tools Hyperion projection system (1920 x 1080 at 60Hz; viewing distance ~113cm) will be employed at Yale MRRC to project stimuli on the mirror fixed to the head coil.

Eye position will be monitored with an MR-compatible EyeLink 1000 Plus (SR Research Ltd., Ottawa, Canada) eye tracker. Only one eye will be recorded in the scanner: the left eye in Donders Institute and the right one in Yale. Pupil and corneal reflection will be sampled at 1000 Hz and analyzed to ensure that participants fixate at the accurate position. The eye tracker will be calibrated at the beginning of each session and repeated between runs if necessary.

Anatomical and functional images will be acquired on a 3T Prisma scanner, using a 32-channel head coil. Anatomical images will be acquired using a T1-weighted magnetization prepared rapid gradient echo sequence (MP-RAGE; GRAPPA acceleration factor = 2, TR/TE = 2300/3.03 ms, voxel size 1 mm isotropic, 8° flip angle). Functional images will be acquired using a whole-brain T2*-weighted multiband-4 sequence (time repetition [TR] / time echo [TE] = 1500/39.6 ms, 68 slices, voxel size 2 mm isotropic, 75° flip angle, A/P phase encoding direction, FOV = 210 mm, BW = 2090 Hz/Px). In addition, a single band reference image will be acquired before each run. To allow for signal stabilization the first three volumes of each run will be discarded. To correct for susceptibility distortions, additional scans using the same T2*-weighted sequence, but with inverted phase encoding direction (inverted RO/PE polarity) will be collected while the participant is taking rest at multiple points throughout the experiments.

#### 2. Magneto-Electroencephalography (M-EEG)

*Electrophysiological data acquisition*. M-EEG recordings will be acquired at the Centre for Human Brain Health (CHBH) of University of Birmingham in the United Kingdom, and at the Center for MRI Research of Peking University (PKU) in China. Both centers have a 306- channel, whole-head TRIUX MEG system from MEGIN (York Instruments; formerly Elekta). The MEG system comprises 204 planar gradiometers and 102 magnetometers in a helmet-shaped array. Simultaneous EEG will be recorded using an integrated EEG system and a 64-channel electrode cap. The MEG system is equipped with a zero boil-off Helium recycling system and the noise-resilient ARMOR sensors and placed in a shielded room (2 layers of mu-metal and 1 layer of aluminum). In order to covers the brain more homogeneously, the MEG gantry will be positioned at 68 degrees.

Prior to each experiment, MEG signals from empty room will be recorded for 3-minutes. We will also record 5-minutes of resting-state data for each participant. M-EEG signals will be sampled at a rate of 1 kHz and band-pass filtered between 0.01 and 330 Hz prior to sampling. The location of the fiducials and the positions of the 64 EEG electrodes will be recorded using a 3-D digitizer system (Polhemus Isotrack). A set of bipolar electrodes will be placed on the subject’s chest (upper left and upper right chest position) to record the cardiac signal (ECG). Two sets of bipolar electrodes will be placed around the eyes (two located at the outer canthi of the right and left eyes and two above and below the center of the right eye) to record eye movements and blinks (EOG). Ground and reference electrodes will be placed on the back of the neck and on the right cheek, respectively. The participant’s head position inside the MEG system will be measured at the beginning and at the end of each run using four head position indicator (HPI) coils placed on the EEG cap. Specifically, the HPI coils will be placed next to the left and right mastoids and on left and right frontal areas. Their location relative to anatomical landmarks will be digitized with a Polhemus Isotrak System. During the measurement, high frequency (>200 Hz) signals are produced by those coils and the localization of these signals is used to estimate the head position in the sensor space. However, the interaction between the signals generated by these coils can be non-linear and produce some artifacts that are difficult to filter out. To avoid this issue, head position measurement will be performed only during resting periods (as opposed to continuously).

Anatomical *MRI data acquisition*. For each subject, a high resolution T1-weighted MRI data (3T Siemens MRI Prisma scanners (32 channel coil) with a resolution of 1 x 1 x 1 mm, 208 sagittal slices; field of view (FOV): 256 × 256 matrix) will be acquired before or after the MEG acquisition to later perform accurate source localization using individual-subject realistic head model.

*Behavioral setup*. In both centers, visual stimuli will be presented on a screen placed in front of the participant with a PROPixx DLP LED projector (VPixx Technologies Inc.) at a resolution of 1920 x 1080 pixels and a refresh rate of 120 Hz. The distance between the subject’s eyes and the screen will vary across the labs (CHBH: 119 cm, PKU: 85) in order to archive in both setups a field of view of 36.6 x 21.2 degrees. In Experiment 2, sounds will be delivered through a set of MEG-compatible earphones (provided by MEGIN) connected to the audio interface of the MEG system. Participants will respond with both hands using two 5-button response boxes (CHBH: NAtA, PKU: SINORAD).

*Eye tracker*. In both centers, eye movements will be monitored and recorded from both eyes (binocular eye-tracking) using MEG compatible EyeLink 1000 Plus eye-tracker (SR Research Ltd., Ottawa, Canada). Nine-point calibration will be performed at the beginning of the experiment, and recalibrated if necessary at the beginning of each block. Pupil size and corneal reflection data will be collected at a sampling rate of 1KHz.

*Source localization*. Source localization will be performed using beamforming (LCMV or DICS) or minimum-norm estimation approach (MNE, dSPM). Source-level analyses will be performed in each subject, co-registered to individual anatomical MRIs using the digitized head surface and anatomical landmarks. Time-resolved multivariate decoding will be performed in the sensor space, from which the decoding weights are obtained for each sensor. Source localization will then be performed on the weight maps to project the decoding results to source space [61]. To verify the cortical source localization for the decoding results in M-EEG, we will examine whether face/object decoding is localized to the corresponding selective areas, e.g., FFA, PPA. In addition, we will consider using fMRI’s decoding results to localize ROIs for M-EEG decoding analysis.

*Inter-subject alignment*. Individual data will first be aligned to a standardized brain template (i.e., the ‘fsaverage’ template) before the group analysis. We plan to use two inter-subject alignment methods and test which one is better during phase 2 (analysis development). One approach is to generate the forward (the leadfield) model with the spacing between the sources constrained to the MNI “fsaverage” brain (i.e., the same number of sources per area independently of the individual differences). The second approach is to create the leadfield model from the individual brain using an even spacing (i.e., the number of sources will depend on the size of each specific areas). Both approaches will be explored and compared during the analysis development stage.

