### Overview of operational hypotheses of the theories

Based on the opposing predictions of the theories, we will focus on testing three predictions. The first refers to **decodability of content of consciousness** (see analysis #1 below). Decoding will be tested for category as well as for orientation (which is a task irrelevant feature, because–as opposed to category–it is completely orthogonal to the task). As the stimuli are clearly visible in this experiment, the theories predict that information about the content of consciousness should be consistently found in the underlying neural substrates, even if the stimulus (or one of its features, like orientation) is task-irrelevant. Thus, according to GNW, such information should be found in nodes of prefrontal areas, while according to IIT it should be primarily found in posterior areas. The critical test of these predictions will accordingly be whether decoding of category and orientation generalizes from the task relevant (non-target) condition to the task irrelevant condition, within the predicted brain regions (PFC for GNW versus posterior hot zone for IIT). The second prediction refers to the **maintenance of a percept over time**, manipulated here via stimuli duration (see analysis #2 below). GNW predicts transient activity, reflecting an updating mechanism at stimulus onset and offset, while IIT predicts that the physical substrate of consciousness should remain in a similar activity pattern throughout the duration of the conscious experience (here, as long as the stimulus was presented). The third prediction focuses on **inter-areal communication** between different cortical regions during conscious perception (see analysis #3 below). GNW and IIT postulate different nodes (topologies) related to consciously perceiving a stimulus: for GNW, long-range synchrony is predicted between prefrontal and category-selective areas in high-level sensory cortex; for IIT synchronization is predicted within the posterior hot-zone, between category-selective regions in high-level sensory cortex and lower-level visual areas. Finally, an additional goal of this experiment is to **pinpoint the putative NCC**, while detecting areas that cannot be regarded as such, as their activity reflects task related processes (see analysis #4 below). This holds implications for the theories, as they differ in their predictions about the NCC (see‘*Neural Activations related to consciousness*’ above).

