### Planned analyses and expected outcomes

#### 1. Multivariate decoding

To test which cortical areas contain information about clearly perceived stimuli across both task-relevant and task-irrelevant conditions, we will decode stimulus category (face/object or letter/false-font) and orientation (side view/front view) in the task-relevant non-target condition and then test for cross-task generalization of decoding to the task-irrelevant condition. Cross-task generalization from task-irrelevant to task-relevant condition will also be tested. Category decoding will always be carried-out within each stimulus class (faces vs. objects and letters vs. false-fonts), rather than between classes which would confound category and task (i.e., we will not decode faces vs. letters, or objects vs. false-fonts). Note that as opposed to information on category, which will sometimes be relevant and sometimes irrelevant, information on orientation will always be task-irrelevant during the entire experiment, despite being clearly seen. As mentioned above, here and in all analyses, we will use the first half of the data to optimize our analyses during phase 2 of the project (analysis development stage), including the selection of optimal decoding schemes (options include: linear SVMs, Bayesian SVMs, LDA, naïve Bayes, K-nearest neighbor, logistic regression, random forest).

GNW predicts that conscious content will be decodable from areas in the prefrontal cortex i.e., inferior frontal gyrus, middle frontal gyrus, and cingulate cortex [21, 51, 52], instantiating the global workspace, both for task relevant and task irrelevant conditions. Thus, GNW would expect transient information about category and orientation to be decodable from the PFC and global-workspace recipient regions in posterior and higher-order sensory cortex in task-relevant conditions, and for decoding to generalize between the task-relevant and task-irrelevant conditions and vice versa, specifically during the 300–500 ms time window. IIT predicts that content-specific NCCs will primarily be found in the posterior hot zone, independent of task-relevance, and makes no specific predictions as to the relevant time window. Thus, decoding of categories and orientations and cross-task generalization of decoding between the task-relevant and task-irrelevant conditions and vice versa should be maximal in posterior cortical areas.

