#### 3. Inter-areal communication: Patterns of synchronization

This analysis will focus on information sharing/integration between different cortical regions for each specific stimulus category.

GNW predicts that conscious perception, regardless of task, relies on long-range information sharing between nodes of PFC and Fusiform Face Area (FFA) when seeing a face, and PFC and Lateral Occipital Cortex (LOC) when seeing an object. This implies that synchronization within these regions should be more consistent across tasks (for a given stimulus category) than across stimuli (for a given task). IIT predicts strong bindings (‘relations’) between category-selective areas and lower-level visual areas, which again should be found regardless of the task. Hence, patterns of synchronization should be found between category-selective regions (FFA and LOC) and early visual cortex: specifically, between FFA and V1/V2 when seen faces (but not other stimulus categories) and between LOC and V1/V2 when seen objects (but not other stimulus categories). This synchronization should be more consistent across tasks than across stimuli.

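### M-EEG decoding is to be localized by source-projecting raw classifier weights, which can be non-zero where there is no class signal, so the M-EEG split between PFC and posterior cortex can be biased

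*Protocol article*

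**What the plan says.** The M-EEG part of the data collection procedures (paragraph on source localization) sets the order of steps. Decoding comes first: "Time-resolved multivariate decoding will be performed in the sensor space, from which the decoding weights are obtained for each sensor". The next step is: "Source localization will then be performed on the weight maps to project the decoding results to source space". A method paper is cited there. The text mentions no conversion of weights into activation patterns. The inverse method stays open between two beamformers and two minimum-norm variants.

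Two safeguards follow. One is a check: "we will examine whether face/object decoding is localized to the corresponding selective areas, e.g., FFA, PPA". The other is tentative: "we will consider using fMRI’s decoding results to localize ROIs for M-EEG decoding analysis".

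The decoder is chosen in phase 2 from a list given under Experiment 1, Multivariate decoding: "options include: linear SVMs, Bayesian SVMs, LDA, naïve Bayes, K-nearest neighbor, logistic regression, random forest".

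Location carries the inference. In the overview of operational hypotheses for Experiment 1, the critical test is whether decoding generalizes across task conditions "within the predicted brain regions (PFC for GNW versus posterior hot zone for IIT". Under Multivariate decoding, the IIT prediction is a maximum in posterior areas, so the relative size of the map in different regions matters. The GNW prediction is tied to 300–500 ms.

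**The concern.** A linear classifier's weights answer the question of how sensors should be combined to separate the classes. They do not answer where the class difference is expressed. A sensor with no class difference earns a weight if it records noise that also contaminates an informative sensor, because subtracting it cleans the signal. The listed inverse methods are built to explain measured field patterns. Given a filter instead, they can place a source where the decoder was only cancelling noise.

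That matters because the GNW prediction needs time resolution, and M-EEG is the time-resolved method with whole-head coverage; iEEG electrode placement is decided on clinical grounds. If the projected map reflects noise cancellation, M-EEG could credit PFC or posterior cortex with content that is not there.

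The planned check does not cover this. It asks whether face/object decoding reaches category-selective areas, all of them posterior. It can succeed while a spurious PFC source remains, and it has no counterpart for orientation or location decoding.

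**Working it through.** The plan gives no figure for this step, so there is nothing to reproduce. The check asks whether the mechanism is real and how large it can be.

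**1. Two sensors, exact.** Assumed inputs: class difference d = (1, 0), so sensor 2 carries no signal; unit noise variances; noise correlation ρ.

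- Noise covariance Σ = [[1, ρ], [ρ, 1]].
- Linear discriminant weights w = Σ⁻¹d = (1, −ρ)/(1 − ρ²), so |w₂/w₁| = ρ.
- Data covariance C = Σ + c·dd′, with c the between-class variance. The activation pattern is Cw = d·(1 + c/(1 − ρ²)), whose second element is 0 for every ρ.

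| ρ | relative weight at no-signal sensor | pattern at no-signal sensor |
|---|---|---|
| 0 | 0 | 0 |
| 0.3 | 0.30 | 0 |
| 0.5 | 0.50 | 0 |
| 0.7 | 0.70 | 0 |
| 0.9 | 0.90 | 0 |

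**2. From sensors to sources, simulated.** All settings are assumptions: 100 sensors, 400 sources, a 1/r² lead field, a noise-normalised minimum-norm inverse, linear discriminant weights, 1,000 trials and 150 runs per setting. The class signal (±0.6) sits at one posterior source only. Background noise has SD 0.3 at each source and at each sensor. Class-free noise is shared between that posterior site and one frontal site, where it enters at full or half size. Relative to the class signal, shared SDs of 1, 3 and 6 are 1/0.6 = 1.7, 3/0.6 = 5 and 6/0.6 = 10 times as large.

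| shared noise SD | frontal size | false frontal peak: weights | false frontal peak: patterns | median frontal/posterior maximum: weights | same: patterns |
|---|---|---|---|---|---|
| 0 | – | 0% | 0% | 0.19 | 0.13 |
| 1 | full | 0% | 0% | 0.58 | 0.14 |
| 1 | half | 0% | 0% | 0.55 | 0.13 |
| 3 | full | 31% | 0% | 0.91 | 0.16 |
| 3 | half | 91% | 0% | 1.49 | 0.14 |
| 6 | full | 40% | 5% | 0.96 | 0.23 |
| 6 | half | 97% | 2% | 1.75 | 0.16 |

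A separate set-up of 200 runs, with strong frontal noise independent of the posterior site, gave no false frontal peak from weights (0%, against 1% for patterns). The weight map was even somewhat cleaner there: median frontal/posterior energy was 0.16, against 0.27. The error therefore needs noise shared between regions.

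**3. Decoders on the list.** K-nearest neighbor and random forest yield no signed linear weight per sensor, so the stated route cannot be carried out for them. Naive Bayes in its usual diagonal Gaussian form ignores noise correlation and gives a sensor without class difference no weight, so the failure in step 1 does not arise there.

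**The case against.** The strongest reply is that the step rests on a cited method paper, which is not at hand. That paper may convert weights to patterns before projection, with weight maps used as shorthand. The article also says openly that it leaves analysis details to phase 2. This limits certainty but does not remove the point. Nearby choices are worded as open (inverse method, inter-subject alignment, decoder), whereas projecting the weight maps is worded as settled.

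Second, size. A reader might infer from a textbook example that a no-signal sensor gets almost the weight of the informative one. A ratio of 0.91, for instance, arises when noise of variance 1 is fully shared and independent noise of variance 0.1 is added to each sensor. That is a correlation of 1/1.1 = 0.91, close to the worst case. The article gives no noise covariance, so no such value can be claimed for this study.

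Third, scope. A reader might infer that the study's whole PFC-versus-posterior answer hangs on this step. The documents do not support that: fMRI and iEEG decoding do not use it, and the timing of sensor-level decoding does not depend on it. Experiment 2 also plans decoding within ROIs as well as across the whole brain, although a positive result from either counts. For M-EEG, fMRI-derived ROIs are only under consideration.

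Fourth, a reader might infer from the naming of PPA that the check cannot verify object decoding. The areas are given as examples, so LOC is not excluded. What stands is an inconsistency of wording. Elsewhere the object area is LOC, as in the Experiment 1 synchronization analysis ("PFC and Lateral Occipital Cortex (LOC) when seeing an object") and in Experiment 2, and the stimuli include no scenes.

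**Conclusion.** The concern holds for the M-EEG localization of decoding, if the step is followed as written with a linear decoder that uses the full covariance. The map can then show regions with no class signal. In the two-sensor case the relative error equals the noise correlation. In the assumed simulations it ranged from no false frontal peak, with no or weak shared noise, to 97% of runs with strong shared noise. Even at a shared SD of 1, where no peak was misplaced, the frontal share of the map was about four times that of the patterns (0.58/0.14 = 4.1; 0.55/0.13 = 4.2).

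The direction and size in the real data are unknown, because they depend on a noise covariance that the article does not give. The conclusion is that the M-EEG attribution can be biased and that the stated check cannot rule this out; it is not that the attribution will be wrong. It also assumes that the cited method does not already include the conversion.

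**What to change.** Before the analysis is locked for phase 3, make one of two changes to the source localization paragraph:

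- State that activation patterns are projected in place of raw weights. These are the data covariance times the weights at each time point, with any scaling or whitening across magnetometers, gradiometers and EEG undone before projection. If the cited method already does this, say so.
- Or base the M-EEG claim about location on decoding from source-reconstructed data within predefined PFC and posterior ROIs. This is required if the chosen decoder has no linear weights, as with K-nearest neighbor and random forest.

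As a minor wording point, name LOC in the localization check, to match the plan's own object area.

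No new data are needed. The first route costs one matrix product per classifier and time point, plus care with sensor scaling. The second costs a further decoding run per ROI. Both can be tried on the first half of the data in phase 2.
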